**Figure 2 F2:**
[figure not shown]
Flow of participants, figure format obtained from the CONSORT (Consolidated Standards of Reporting Trials) 2010 statement.^a^Complete teacher survey if applicable.

The TAU group will receive standard services and support currently available in the community and complete the same study assessment follow-up. If the parent consented to teacher participation, researchers approach schools for consent to contact the child’s teacher and then mail the teacher a baseline survey to complete.

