**Methods and analysis:**

The RCT aims to recruit 234 children with a diagnosis of ASD, aged 5–13 years, who experience moderate to severe sleep problems. Participants are recruited from paediatrician clinics in Victoria, Australia, and via social media. Families interested in the study are screened for eligibility via phone, and then asked to complete a baseline survey online, assessing child sleep problems, and child and family functioning. Participants are then randomised to the intervention group or treatment as usual comparator group. Families in the intervention group attend two face-to-face sessions and a follow-up phone call with a trained clinician, where families are provided with individually tailored behavioural sleep strategies to help manage the child’s sleep problems. Teacher reports of sleep, behavioural and social functioning are collected, and cognitive ability assessed to provide measures blind to treatment group. The primary outcome is children’s sleep problems as measured by the Children’s Sleep Habits Questionnaire at 3 months post-randomisation. Secondary outcomes include parent and child quality of life; child social, emotional, behavioural and cognitive functioning; and parenting stress and parent mental health. Cost-effectiveness of the intervention is also evaluated.

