### Patient involvement

The intervention used in this study is based on the ADHD *Sleeping Sound* trial, during which participant feedback on the acceptability and feasibility of the study was collected.^47^ There were no reported concerns from participants.^47^ In this trial, we will be collecting feedback data about the program from parents.

### Recruitment: stage 1

*Recruitment through Victorian paediatric clinics*. Victorian paediatricians identified potential participants meeting inclusion criteria, whom they have seen in the last 12 months, and sent a letter inviting them to participate in the study. Study advertisements were also displayed in the waiting areas of clinical services and disseminated widely through research, clinical and community-based networks available to investigators.

### Recruitment: stage 2

The research team telephoned all primary parents who registered interest in the study to assess inclusion/exclusion criteria (approximately 25 min phone call). Eligible families were provided with an information sheet, consent form (see online supplementary appendix) and baseline survey by email or post. The child’s primary parent was asked to complete the survey and consent form. Online surveys were completed via a secure research database REDCap.^54^ Once parents provided written consent, they were asked to provide diagnostic and cognitive assessment reports where available. If optional consent was provided to contact the child’s school teacher, a link to an online survey was sent to the child’s nominated teacher.

10.1136/bmjopen-2019-029767.supp1Supplementary data

Families are sent a separate hardcopy consent form for researchers to access the child’s Medicare Benefits Scheme (MBS) and Pharmaceutical Benefits Scheme (PBS) data for cost-effectiveness analysis. Medicare collects information on the child’s doctors’ and allied health professionals’ visits and the associated costs (including out-of-pocket costs). PBS collects information on prescription medications which have been recorded at pharmacies.

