### Randomisation

The flow of participants from recruitment to follow-up assessments is displayed in figure 2. Participants are randomised to either the intervention or TAU groups by an independent research assistant once consent forms and baseline surveys have been completed. Treatment allocation is determined sequentially, according to a computer-generated block randomisation sequence with 1:1 ratio between groups, with blocks of randomly varying size (4, 6 and 8) developed by an independent statistician who is not involved in the project. The independent statistician will then upload this randomisation list into REDCap,^54^ a secure research database, to ensure allocation concealment. Given the relatively fewer diagnoses of ASD among girls,^55^ randomisation is stratified by gender to ensure equal representation of girls, boys and other genders (ie, transgender, intersex) in both study arms. Siblings are eligible to participate in the study provided they each meet all inclusion criteria. Families with siblings enrolled in the study are randomised in sequence based on the return of the primary parent baseline surveys, with all subsequent siblings allocated to the same treatment group. All families are sent a letter informing them of their group allocation and are not able to enrol further siblings once notified of group allocation. A study clinician then telephones intervention families to book the intervention sessions.

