### Data analysis

Primary analysis will be intention-to-treat (within participant data included as per initial treatment group allocation, regardless of actual intervention received) and will compare outcomes of children in the TAU and intervention groups at the 3- and 6-month post-randomisation time points, though our primary endpoint is 3 months post-randomisation. Analysis of the primary outcome (ie, child sleep problems) and all secondary outcomes (child—teacher reported daytime sleepiness, sleep hygiene, emotional and behavioural problems, social communicative symptoms, cognitive performance, academic achievement, school attendance and quality of life; parent—parenting stress, mental health, quality of life and work attendance) will be carried out using linear mixed effects regression with results presented as mean differences (and 95% CIs). For each outcome, a single mixed-effects model will be fitted incorporating baseline, 3-month and 6-month data using random effects to allow for the repeated measures within an individual, and clustering of individuals within the child’s paediatrician. Separate parameters will be estimated for group differences at 3-month and 6-month postintervention; scores at baseline are added as a covariate. Differences in the outcomes of intervention and TAU groups will be assessed with linear mixed models, with individuals clustered within the child’s paediatrician and assessment times clustered within individuals. We will run an unadjusted model and compare this to an adjusted model, with the unadjusted model as our primary analysis, and adjusted results to evaluate robustness of these findings. The adjusted model will include the following as covariates: child gender, age, ASD symptom severity (measured using the Social Communications Questionnaire—current form,^53^ medication use (obtained from the Resource Use Questionnaire) and SES (measured according to the families residential postal code and using the index of relative socioeconomic disadvantage).^47 59^ The child’s paediatrician and individual participant will be modelled as random effects and the remaining variables will be handled as fixed effects. To account for missing data, the mixed models will be fitted using conditional maximum likelihood. As this approach makes an untestable assumption that data are missing at random, we will perform sensitivity analyses in the form of pattern mixture models to explore the effect of departure from this assumption. A per-protocol analysis will also be undertaken as a supplementary analysis. Significance will be tested at p<0.05 for the primary analysis, but adjustments for type I error inflation will be made for secondary outcomes by using the false discovery rate method.^60^

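### The timing of the teacher baseline relative to allocation is described inconsistently, yet the teacher outcomes are adjusted for that score

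*Protocol article*

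**What the plan says.** Four parts of the Protocol article bear on when the teacher baseline is collected.

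- **Recruitment: stage 2.** Teacher participation is optional, and the survey is electronic: "If optional consent was provided to contact the child’s school teacher, a link to an online survey was sent". This stands before the Randomisation section.
- **Randomisation, main text.** Allocation is made "by an independent research assistant once consent forms and baseline surveys have been completed". Whose surveys count is not said. For sibling families the order is fixed by one survey only; they are "randomised in sequence based on the return of the primary parent baseline surveys". The section then describes the letter announcing the group and the clinician's call to book sessions.
- **Randomisation, paragraph after Figure 2.** Where the parent has agreed to teacher involvement, researchers first seek the school's agreement and "then mail the teacher a baseline survey to complete". This is a paper survey with an extra consent step. No date or order relative to allocation is given.
- **Abstract.** The family completes its baseline survey, and "Participants are then randomised to the intervention group or treatment as usual comparator group". Teacher reports are mentioned afterwards, without timing.

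On use of the score, the Data analysis section applies one model form to the primary and all secondary outcomes, naming teacher-reported daytime sleepiness among them, and "scores at baseline are added as a covariate". Table 3 lists the teacher sleepiness questionnaire and the teacher version of the Strengths and Difficulties Questionnaire at baseline, 3 months and 6 months. The Measures section presents teacher reports as blinded measures, because families cannot be blinded.

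**The concern.** The two descriptions of the teacher survey differ in mode (link or post), in gatekeeping (the parent's consent, or the school's as well) and in where they fall in the account of trial conduct. An optional survey cannot be a condition of randomisation for every child. School consent followed by posting takes time, while session two comes 2 weeks after session one and the phone call 2 weeks after that. Part or all of the programme could therefore have been delivered before a teacher returns a survey labelled baseline.

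If that happens, the covariate is no longer a pre-treatment variable. In the intervention arm it already contains some of the treatment effect; in the usual-care arm it does not. Adjusting for it removes that part of the effect from the estimate.

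The teacher reports matter because the primary outcome is reported by parents who know their allocation. Of the measures the article names as blinded, they are also the only ones that Table 3 marks at 3 months, since the child tests are scheduled at 6 months only.

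**Working it through.** **1. The plan's own figure.** Inputs from the Sample size section: standardised difference 0.5, SD 1, two-sided 5% level, 80% power, ICC 0.08 with mean cluster size 4, within-person ICC 0.20, attrition 20%.

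- Unadjusted: 2 × (1.960 + 0.842)² / 0.5² = 62.8 per arm.
- Adjusted: 62.8 × [1 + (4 − 1) × 0.08] × [1 + (2 − 1) × 0.20] / (1 − 0.20) = 62.8 × 1.24 × 1.20 / 0.80 = 116.8, so 117 per arm and 234 in total.

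The stated figure reproduces. It does not use the teacher survey, so this point leaves it unchanged.

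**2. Whether the text settles the timing.**

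| Part of the article | Points to |
|---|---|
| Recruitment: stage 2 (link on parental consent) | sent before allocation; return not required |
| Randomisation, general rule (baseline surveys complete) | before allocation, if teachers' surveys are meant |
| Randomisation, sibling rule | parent survey only |
| Abstract | family survey, then randomisation |
| Paragraph after Figure 2 (school consent, then post) | no stated timing; follows the allocation steps in the text |

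No line fixes the teacher survey before allocation, and none fixes it after.

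**3. Size of the possible bias.** Let d be the true effect, b the slope of follow-up on baseline, f the share of the effect already present when a late baseline is taken, and q the share of baselines that are late. The late scores create a between-arm difference of about f × q × d in the covariate. The adjusted estimate is then about

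d − b × (f × q × d) = d × (1 − b × f × q).

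The article gives none of b, f or q for teacher scores. The range below is assumed. Its lower slope equals the only within-person correlation in the article (0.20, not teacher-specific). For illustration d = 0.5, the planning effect for the sleep questionnaire, and q = 1 (all late).

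| b | f | Estimate 0.5 × (1 − b × f) | Shrinkage | Simulated estimate | Power at 63 per arm |
|---|---|---|---|---|---|
| any | 0 | 0.500 | 0% | 0.500 to 0.501 | 80% |
| 0.2 | 0.25 | 0.475 | 5% | 0.473 | 76% |
| 0.2 | 0.5 | 0.450 | 10% | 0.453 | 71% |
| 0.5 | 0.25 | 0.4375 | 12.5% | 0.435 | 69% |
| 0.5 | 0.5 | 0.375 | 25% | 0.378 | 56% |
| 0.7 | 0.25 | 0.4125 | 17.5% | 0.410 | 64% |
| 0.7 | 0.5 | 0.325 | 35% | 0.329 | 45% |

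The simulation (400,000 children per setting, effect signs dropped) agrees with the formula. Shrinkage scales with q: with half the baselines late, the 10% row becomes 0.2 × 0.5 × 0.5 = 5% and the 35% row becomes 17.5%.

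The power column is a guide only. It uses the 63 evaluable children per arm from step 1 and an unadjusted 5% level. It ignores the precision gained from a covariate, the smaller teacher sample and the false discovery rate adjustment.

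**The case against.** A reader might infer that the article places the teacher survey after allocation and that the teacher effects will be attenuated. The text does not support that. The paragraph after Figure 2 gives no date. It concerns usual care and is not written as a timeline, since it mentions follow-up before baseline. Recruitment: stage 2 points to the period before randomisation, and the baseline surveys named in the general rule can be read to include the teacher's. Link and post could both have been used, since the Data management section provides for hardcopy surveys. Figures 1 and 2 are not available here and may show the timing; a note to Figure 2 mentions the teacher survey. All of this stands, and it limits the point to an inconsistency with a possible consequence.

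On size, a survey returned after the letter but before session one carries no treatment effect, so the bias may be nil. That also stands, and zero belongs in the range.

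It can be said too that handling of late baselines belongs in a statistical analysis plan. A missing visit window alone would indeed be no finding. Here, however, the article itself gives conflicting accounts of the survey and itself fixes the score as a covariate.

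A late survey also leaves more time for a family to disclose its group. The Measures section already asks parents not to tell teachers, and the same risk applies at 3 and 6 months, so no weight is put on it.

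Finally, a date filter might exclude different children in each arm. A cut-off at notification avoids this in the main: families do not yet know their arm, so it should not influence whether the survey is back by then.

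**Conclusion.** The point holds as one of unclear timing with a possible bias. The article does not establish that teacher baselines precede treatment, and it adjusts the teacher outcomes for them. If some were completed after treatment had begun to act, the adjusted teacher comparisons could be biased towards no effect. The relative size is zero if none were, and about 5% to 35% if all were, with an assumed slope of 0.2 to 0.7 and a quarter to a half of the effect already present. These inputs are assumptions; the article gives no survey dates and no teacher-score correlation.

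The scope is the teacher-reported secondary outcomes. The parent-reported primary outcome, the sample size and the child tests, which have no baseline in Table 3, are not touched. The matter is worth settling before analysis, because a falsely small teacher effect could be read as blinded evidence against a parent-reported benefit.

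**What to change.** - Reconcile Recruitment: stage 2, the general rule under Randomisation and the paragraph after Figure 2. State how and when the teacher baseline is collected, and whether it must be complete before allocation.
- In the teacher-outcome models, use a teacher score as the baseline covariate only if it is dated before the family is notified of allocation. Treat later scores as missing baseline and keep the child in the model, through a missing-indicator or a joint model.
- Report the number of late teacher baselines by arm.
- Add a sensitivity analysis of the teacher outcomes without baseline adjustment.

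Follow-up was still in progress when the article was written, so this needs only a check of survey dates (receipt dates for posted forms) and a few sentences in the analysis section. The price is a small loss of precision. Part of it comes from setting aside surveys completed after the letter but before the first session, which would have been valid.

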### Intervention group

*Delivery of the sleep intervention*. The behavioural sleep intervention is delivered by study-employed clinicians (paediatrician or psychologist experienced in working with children with ASD). Clinicians were trained over two × 3-hour interactive sessions (by HH and ES), have a detailed program manual and meet fortnightly to ensure fidelity to the program. The intervention consists of two 50 min face-to-face consultations and one follow-up phone call at 2-week intervals. The content of the original *Sleeping Sound* ADHD intervention^47^ has been adapted to children with ASD to include specific visual aids and social stories to assist in the delivery of the sleep intervention for this population.^56^ Intervention sessions are held in rooms at one of our study sites (Deakin University or The Royal Children’s Hospital) or the treating paediatrician’s consulting rooms, based on family preference.

The behavioural sleep interventions are individually tailored for the child and the family. The strategies that suit the family situation and learning style of the child with ASD are given emphasis. Delayed sleep phase, early morning waking and prolonged night waking (eg, waking overnight where the child is unable to fall back to sleep for an hour or more) are treated with bedtime fading (ie, the child’s bedtime is temporarily set later and gradually brought forward), as well as early morning light exposure. Need for parental presence at sleep time is managed for sleep-onset association using a ‘camping out’ method. Camping out involves parents gradually withdrawing themselves from the child’s bedroom over a period of time. Parent management strategies are used for bedtime resistance and can include use of a ‘bedtime pass’, whereby the child can only leave the bedroom once before sleep and may be coupled with a reward system. Primary insomnia (insomnia with no other established cause) is managed using relaxation training and restricting time in bed (ie, bedtime fading or getting out of bed and doing a relaxing activity if the child cannot fall asleep). In addition to relaxation training, examples of some strategies used to manage anxiety-related insomnia include discussing fears during the day rather than just before bedtime, encouraging the child to stay in bed and rewarding brave behaviour. Visual strategies, such as social scripts and visual timetables, are used to reinforce learning.

*Session One* focuses on an assessment of the child’s sleep problems, psychoeducation about normal sleep and sleep cycles, good sleep habits, and a tailored sleep management plan specific to the sleep diagnosis of the child. As the Sleeping Sound intervention is individually tailored to children and families, participants are encouraged to provide input in relation to goal setting and the interventions they would like to try to assist in managing the sleep problems. Families receive written handouts, summarising session content and complete a written management plan with the clinician. A standardised consultation record is kept for all children including the presenting sleep problem(s), possible contributors to the problem (eg, TV in bedroom), medication use, comorbidities and bedtime routines. Clinicians record the duration of each consultation, sleep problem diagnoses, family sleep management goals, handouts given to parents and management options selected. Sleep problem diagnoses made may include one or more difficulties getting to sleep (sleep anxiety, bedtime resistance, sleep association onset disorder, delayed sleep phase or insomnia) and/or night waking problems (prolonged night waking or early morning waking). Parasomnias (nightmares, night terrors, sleep walking) are recorded, and psychoeducation and general management advice about parasomnias is provided, although these are not a focus of behavioural intervention.

*Session Two* is held 2 weeks later to review the sleep management plan (which includes a sleep diary), reinforce strategies, troubleshoot and monitor progress.

A *follow-up phone call* is conducted 2 weeks after the second visit to answer any further parent questions, reinforce strategies, troubleshoot and monitor progress.

Participants are able to withdraw from the intervention at any time. Participants are asked for feedback of the intervention at all intervention sessions, including follow-up, and this is documented by clinicians to manage any unintended adverse effects of the trial.

### Measures

Study measures are summarised in table 3 below. Additional information collected at baseline includes family and child demographics such as socioeconomic status (SES) and medical data (ie, diagnosed comorbidities). Medication information is captured at baseline and 3- and 6-month follow-up. Based on prior work with children with ADHD and ASD we do not anticipate any risks, side-effects or discomfort to participants in completing our measures. In the event that a parent becomes distressed when completing questionnaires related to stress or mental health, we have included information to link participants to a psychologist on our research team as well as directing parents to contact their general practitioner.

**Table 3 T3:** Summary of measures included in the study

Outcomes	Measure	Source	B	3	6
**C** **HILD OUTCOMES**					
Sleep problems	**Children’s Sleep Habits Questionnaire (CSHQ**). 33-item validated measure of sleep that can distinguish clinical from community samples.^49^ Provides a measure of total sleep problems and eight subscale scores reflecting major behavioural sleep disorders (bedtime resistance, sleep-onset delay, sleep duration, sleep anxiety, night waking, parasomnias, sleep-disordered breathing, daytime sleepiness).	Parent	●	●	●
Sleep hygiene	**Sleep Hygiene Scale**. 7-item study developed measure adapted from the Bedroom Routines Scale.	Parent	●	●	●
Daytime sleepiness	**Teacher Daytime Sleepiness Questionnaire**. 10-item validated scale of daytime sleepiness at school.^68^	Teacher	●	●	●
Social communication functioning	**Social Communication Questionnaire (SCQ) Current** form. 40-item measure of ASD symptoms in past 3 months to measure change in ASD social communication symptoms over time.^53^	Parent	●	●	●
Emotional and behavioural disturbance	**Developmental Behavioural Checklist (DBC**). 96-item measure of emotional and behavioural disturbance in children.^69^ Provides a rating of overall behavioural disturbance and five subscales: disruptive/antisocial behaviour, self-absorbed, communication disturbance, anxiety and ASD social relating.	Parent	●		●
Behavioural and social functioning	**Strengths and Difficulties Questionnaire (SDQ**). 25 items assessing the following subscales: hyperactivity/inattention, conduct problems, emotional symptoms, peer relationship problems and prosocial behaviour.^70^	Parent and teacher	●	●	●
Quality of life	**Child Health Utility 9D (CHU9D**). 9-item measure of child quality of life.^62^	Parent	●	●	●
School attendance	**School attendance** over the preceding 3 months.	Parent	●	●	●
Academic functioning	**Wide Range Achievement Test 4 (WRAT**). Spelling and math computation subtests to assess academic functioning.^71^	Child			●
Academic functioning	Permission to access **NAPLAN** results (Years 3, 5, 7). NAPLAN is a national assessment of literacy and numeracy Australian children complete in Grades 3, 5, 7 and 9.	Linkage			
Cognitive functioning	**NIH Toolbox**. Cognitive Domain Tasks to assess cognitive functioning.^72^ iPad administered assessment of executive function, attention, episodic/working memory, processing speed, language abilities, new learning and reading.	Child			●
